|                                                | Time window                                                       | day -30 to -2 |     |    |    | ± 1 day | ± 3 days | ± 5 days | ± 7 days | ± 7 days | ± 14 days            | ± 1 month | ± 1 month | ± 1 month | ± 1 month |
|                                                | Procedure                                                         |               |     |    |    |         |          |          |          |          |                      |           |           |           |           |
| 1.                                             | Medical /surgical/ history                                        | x             |     |    |    |         |          |          |          |          |                      |           |           |           |           |
| 2.                                             | Ocular / surgical/ history                                        | x             |     |    |    |         |          |          |          |          |                      |           |           |           |           |
| 3.                                             | BMI                                                               | x             |     |    |    |         |          |          |          |          | x                    |           |           |           |           |
| 4.                                             | Vital signs                                                       | x             | x   | x  | x  | x       | o        | o        | o        | o        | x                    | o         | o         | o         | o         |
| 5.                                             | Urine pregnancy test                                              | x             | x   |    |    |         | x        | x        | x        | x        | x                    |           |           |           |           |
| 6.                                             | Hematology/basic chemistry/urine analysis                         | x             | o   | o  | o  | x       | x        | o        | o        | x        | x                    | x         | x         | x         | x         |
| 7.                                             | CRP, IgG, IgM                                                     | x             |     |    | x  | x       | x        | x        | o        | o        | o                    | o         | o         | o         | o         |

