## **3. Study Plan**

### **3.1. Study Design**

This is an open mono-center trial with fellow-eye comparison. Three patients will be assigned to three consecutive, increasing dosage groups (see figure 3):

4) low dose:  $\leq 1 \times 10^{10}$  vgp (n=3)

Between each injection (between patient 1 and 2 and patient 2 and 3) a safety interval of 4 weeks will be kept.

After collection of data on study visit Day 30 of all three patients of the dose cohort and before the scheduled start of the next injections of the consecutive dosage group the DMC will meet and evaluate safety data. If no safety concerns are reported the next dosage group of patients will be treated as scheduled. DMC advice may also result in a dose reduction for the next dosage cohort.

5) intermediate dose:  $\leq 5 \times 10^{10}$  vgp (n=3)

Between each injection (between patient 4 and 5 and patient 5 and 6) a safety interval of 4 weeks will be kept.

After collection of data on study visit Day 30 and before the scheduled start of the next injections of the consecutive dosage group the DMC will meet and evaluate safety data of groups 1 and 2. If no safety concerns are reported the next dosage group of patients will be treated as scheduled. DMC advice may also result in a dose reduction for the next dosage cohort. Within the high dose cohort, the interval between injections / individual patients will be four weeks.

6) high dose:  $\leq 1 \times 10^{11}$  vgp (n=3)

Between each injection (between patient 7 and 8 and patient 8 and 9) a safety interval of 4 weeks will be kept.

The following figure (Fig. 3) explains the schedule and timelines of dose groups and the points of decisions of the data monitoring committee.

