## Dosage/Dose Regimen for rAAV.hCNGA3 Phase I Trial

[figure not shown]

Figure 3: Schedule of dosing groups and intervals

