#### *(3) Immune reactions and/or toxic effects on retinal function caused by AAV8-CNGA3*

Due to the time required for transgene expression following subretinal delivery of AAV8, it is unlikely that any toxic effects of the transgene product would be evident prior to at least two weeks after surgery at the earliest. These might include similar immune reactions as described in (2) above. Also any toxic effects of AAV8-CNGA3 on visual function might be manifest by a worsening of visual acuity after the initial period of post-operative recovery. Potential toxic effects on retinal function are likely to be manifest as a significant drop in visual acuity (defined by 15 letters or more).

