### 7.3.1. Reporting Procedures for Serious Adverse Events

The Data Monitoring Committee (DMC) will review all SAEs for the study at certain time-points of the trial. The DMC is detailed in Appendix B and may hold personal /TC/electronic meetings. The DMC will meet at regular intervals and consider:

- Occurrence and nature of adverse events
- Whether additional information on adverse events is required
- Consider taking appropriate action where necessary to halt the trial (see below)
- Act / advise on incidents occurring between meetings that require rapid assessment (e.g. SUSARs)

Especially before the second and third trial cohort, when the Day 30 results for each patient are available, the DMC must meet and make a go/no-go decision for the treatment of the next dose cohort, which needs to be reported to the PI as soon as possible.

All SAEs will be reported to the DMC within one day of discovery or notification of the event. All SAE information will be recorded on an SAE form, which will be sent electronically to members of the DMC. Additional information received for a case (follow-up or corrections to the original case) will be detailed on a new SAE form.

The CRO will – on behalf of the Sponsor - report all AEs, SAEs and SUSARs to the Ethics Committee and the Regulatory Authority (PEI) in an annual safety report. Fatal or life-threatening SUSARs will be reported within 7 days and all other SUSARs within 15 days. The PI will also inform all members of the study group on all adverse events that might affect the safety of participants.

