| cataract formation                           | 1-5%                                               | 9%                     | 10-20%                               |
| transient intraocular hypertension           | 5%                                                 | 0%                     | 5%                                   |
| corneal erosion                              | 5-20 %                                             | 5-20 %                 | 5-20 %                               |

**Table 2:** Risks of complications during 23g PPV referring to literature, previous NHP studies and expected rates for the planned trial. [1] Wilkinson et al., 2013 [2] Lee et al., 2012 [3] Wykoff et al., 2010.

Regarding 2) there is a risk for a loss of vision due to ophthalmic immune reactions to the vector (indirect) or due to direct effects of the vector (however, pre-clinical

[figure not shown]

studies showed no toxic effects with up to 10 fold higher concentrations). If any immune reaction should be triggered by the vector, this might include non-infectious inflammation of the pigment epithelium (epitheliitis), retina (retinitis), vitreous cavity (vitritis) or uveal tissue (uveitis). None of these have been reported in any previous clinical trial involving AAV in ocular gene transfer.

Such effects may result in a significant deterioration of visual function (decrease in VA of  $\geq 15$  letters) and might also occur after initial improvement. A vulnerable period for direct and/or indirect (immunogenic) effects due to the viral packaging protein of the vector would be the first two weeks (time of concomitant steroid treatment). No clinical trial has as of yet reported immune-reaction to the transgene (even in systemic gene transfer). It therefore seems unlikely that a direct or indirect effect due to transgene expression would occur after ocular gene transfer in the immune-privileged subretinal space.

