#### 8.4.27. Systemic steroids

Systemic steroids will be given orally at 1.0mg/kg for approximately 3 weeks starting at day -1 and then tapered off after day 19 at the discretion of the investigator (e.g. 40/30/20/15/10mg).

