## 2. Dosing

In the proposed clinical trial, patients will have one of three dosages injected into a preformed subretinal space with a maximal total volume of 1ml of balanced salt solution (BSS):

- Low dose:  $\leq 1 \times 10^{10}$  vector genome particles (vgp)
- Intermediate dose:  $\leq 5 \times 10^{10}$  vgp
- High dose:  $\leq 1 \times 10^{11}$  vgp

The two important parameters are the number of vector genome containing particles (vgp) and the number of target cells, which are brought in physical contact with the vector solution. Previous studies targeting the RPE have applied  $1 \times 10^{10}$  to  $1.5 \times 10^{11}$  rAAV2/2 vgp into the subretinal space. The only published trial using the same vector design of the proposed study (rAAV2/8) used significant higher doses ( $1-2 \times 10^{14}$  vgp) to target hepatocytes, and were injected into systemic circulation rather than the confined subretinal space in the eye. Yet, no SARs were recorded in this trial.

[figure not shown]

Vandenberghe et al. showed local toxic effects (degeneration and inflammation) in non-human primates after subretinal injection of  $1 \times 10^{11}$  vgp AAV2/8. However, these AAV particles were not manufactured to GMP or even GLP guidelines and used undiluted in this cohort. Also, cytotoxic GFP was used as reporter-transgene under the control of a highly active CMV promoter likely contributing to the toxic effects observed.

Our toxicology study has shown no adverse reaction at the level of the highest dose planned in the clinical trial ( $\leq 1 \times 10^{11}$  vgp) and only transient reactions were observed in 2/4 animals with a ten-fold higher dose ( $1 \times 10^{12}$  vgp) with no residual changes were observed 90d post dosing. We therefore conclude that it seems safe to apply a maximal dose of  $\leq 1 \times 10^{11}$  vgp in our patients. This dose was therefore chosen as the maximal dose.

This dosing range was chosen based on pre-clinical evidence in the CNGA3-ko mouse model. Michalakakis et al. showed successful rescue by injecting  $5 \times 10^9$  rAAV2/5 into the subretinal space detaching ca. 1/3 of the retina [1]. This was again confirmed with the IMP vector (engineering lot) using a dose as low as  $5 \times 10^9$  vgp in a relevant mouse model (see Study report).

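### In the visible text, the 4-week gap between patients in a cohort does not require the preceding patient's Day 30 examination before the next injection

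*Supplement*

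**What the plan says.** Section 3.1 sets the within-cohort spacing as a time span, in the same words for each dose level. For the low dose it reads: "Between each injection (between patient 1 and 2 and patient 2 and 3) a safety interval of 4 weeks will be kept". It names no visit, data review or decision.

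The conditional step sits between cohorts. Under 3.1, the DMC evaluates safety after the Day 30 data of a cohort have been collected and before the next dose group starts. Section 7.3.1 says that "the DMC must meet and make a go/no-go decision for the treatment of the next dose cohort".

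The Flowchart and section 8.2 place Visit 6 at D14 ±3 days and Visit 7 at D30 ±5 days, with no visit between. Both include BCVA, the basic ophthalmological examination (slit lamp, 8.4.11), funduscopy and OCT as required procedures.

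Section 7.2.3 says of late effects that "it is unlikely that any toxic effects of the transgene product would be evident prior to at least two weeks after surgery". Oral steroid is given at "1.0mg/kg for approximately 3 weeks starting at day -1 and then tapered off after day 19" (8.4.27). Stopping rule 1 in 7.4 is a measured acuity loss of more than 15 letters attributed to the vector.

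Section 3.1 also refers to "Figure 3: Schedule of dosing groups and intervals" for timelines and DMC decision points. That figure is not shown in the text available.

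**The concern.** A staggered start in a first-in-human trial is meant to let one patient's outcome inform the decision to dose the next. Here the stated stagger is slightly shorter than the time to the nominal visit that would supply that information. A site that follows 3.1 exactly can inject the next patient at Day 28, with the preceding patient's Visit 7 two days away.

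The last scheduled look is then Visit 6. It falls at about the earliest time at which the protocol expects transgene toxicity, and while oral steroid is still at full dose. Section 7.2.3 expects such toxicity to appear mainly as a drop in acuity of 15 letters or more, so BCVA is the main detector, and BCVA is not scheduled again until Visit 7. A loss of acuity or an inflammation that starts after Visit 6, and that the patient does not report, could be found only after another patient has received the same dose.

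**Working it through.** The protocol gives no calculation on this point. The check is calendar arithmetic on its own windows.

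**Inputs**
- Within-cohort interval: 4 weeks = 28 days (3.1).
- Visit 6: D14 ±3 = D11 to D17. Visit 7: D30 ±5 = D25 to D35 (Flowchart, 8.2). A visit may take two consecutive days (section 8), so Visit 7 may end on D36.
- Full-dose oral steroid: day -1 to about day 19 (8.4.27).
- First visits: November 2015 to November 2016 (3.2). Screening: D-30 to D-2 (5.1).

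**Visit 7 against a Day 28 injection**
- Earliest: 25 − 28 = −3 days (before).
- Nominal: 30 − 28 = +2 days (after).
- Latest: 35 − 28 = +7 days, or 36 − 28 = +8 if split over two days.
- Of the 11 permitted days, 3 fall before Day 28, 1 on it and 7 after it. This counts what is permitted. It is not a probability.

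**Age of the last scheduled examination when Visit 7 comes after**
- 28 − 17 = 11 days to 28 − 11 = 17 days (28 − 14 = 14 at nominal timing).
- D11 to D17 lies wholly before the taper that starts after day 19.

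**Which injections are affected**
- Two within-cohort steps in each of three cohorts: 3 × 2 = 6 injections (patients 2, 3, 5, 6, 8, 9). At each, the immediately preceding patient may not have had Visit 7.
- Patients 3, 6 and 9 are injected no earlier than 2 × 28 = 56 days after the first patient of their cohort, whose Visit 7 is over by D36. So one Visit 7 at that dose already exists.
- That leaves patients 2, 5 and 8 with possibly no completed Visit 7 at their dose. For 5 and 8, the DMC has already reviewed Day 30 data from the lower dose or doses.

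**Delay from requiring Visit 7 first**
- Per step: 0 days if Visit 7 is done by D28, 2 at nominal timing, 7 to 8 at most.
- Over six steps: 6 × 2 = 12 days nominal; 6 × 7 = 42 to 6 × 8 = 48 at most.

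**First to last injection, with six within-cohort and two between-cohort steps, and no DMC time or replacements**
- Now, nominal: 6 × 28 + 2 × 30 = 228 days.
- With the condition, nominal: 8 × 30 = 240 days.
- With the condition, every Visit 7 ending on D36: 8 × 36 = 288 days.

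**Room in the calendar**
- Shortest reading of 3.2: 30 November 2015 to 1 November 2016 = 337 days. Longest: 1 November 2015 to 30 November 2016 = 395 days.
- Screening leads can differ by 30 − 2 = 28 days, so the shortest reading leaves at least 337 − 28 = 309 days.
- Without replacements: 309 − 240 = 69 days spare at nominal timing, and 309 − 288 = 21 with every visit late. DMC meetings must come out of this.
- With both permitted replacements (3.4), assuming each adds one full step: 240 + 2 × 30 = 300 days, leaving 309 − 300 = 9. With every visit late: 288 + 2 × 36 = 360 days, which exceeds 309. The longest reading gives 395 − 28 = 367 days and still holds both.

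**The case against.** The strongest objection is that this argues from silence while the relevant exhibit is missing. Figure 3 concerns dosing groups and intervals, and it may show that each patient's Visit 7 precedes the next injection. That stands as a limit on certainty. However, 3.1 and 7.2.2 describe the figure in terms of dose-group timelines and DMC decision points, which matches the cohort-level rule in the text and does not suggest a patient-level one.

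Second, four weeks reads naturally as a minimum. One site controls both dates and may do Visit 7 on D25 to D28 or wait longer than 28 days. The recruitment period averages about 42 to 49 days per step (337/8 to 395/8), so nothing forces 28-day spacing. This also stands: the overlap is permitted, not prescribed.

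Third, the protocol's own risk assessment points elsewhere. Section 7.5 says that "A vulnerable period for direct and/or indirect (immunogenic) effects due to the viral packaging protein of the vector would be the first two weeks", a period covered by three days in hospital and visits through D14. The same section calls a transgene effect unlikely. Appendix 1 adds: "Our toxicology study has shown no adverse reaction at the level of the highest dose planned in the clinical trial". SAEs go to the DMC within one day (7.3.1), the 7.4 rules apply throughout, and patients carry contact cards for self-reporting (7.5). These points narrow the concern considerably. They do not remove it, because each between-visit safeguard acts only once someone has noticed an event, and the routine adverse-event questions are asked at study visits (8.4.34).

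A reader might infer that six patients are dosed with no Day 30 information at their dose, or that dosing proceeds unmonitored. The documents support neither. Patients 3, 6 and 9 always follow at least one Visit 7 at the same dose, and the safeguards above run without a visit.

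**Conclusion.** The point holds as a modest gap that should be fixed, with moderate confidence. In the visible text of version 5.0, the within-cohort interval is not tied to any examination, and an injection at exactly four weeks can precede the preceding patient's Visit 7. What remains exposed is an effect that begins after Visit 6 and is not reported between visits. At nominal timing it would be found about two days too late for the next patient. The protocol already treats Day 30 data as the evidence needed to start the next cohort, and at nominal timing the within-cohort interval stops just short of it.

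This rests on three assumptions: that Figure 3 adds no patient-level condition, that the next injection is given at or near Day 28, and that Visit 7 is not brought forward. It gives no expected frequency and does not suggest that harm occurred. Nor should a reader infer that placing Visit 7 first would guarantee observation off steroid. The taper starts after day 19 at the investigator's discretion and may still be running at Visit 7.

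**What to change.** State in 3.1 that the next injection within a cohort takes place no earlier than 4 weeks after the previous one, and only after the preceding patient's Visit 7 BCVA, slit-lamp examination, funduscopy and OCT are complete and have been reviewed against the stopping rules in 7.4. If Figure 3 already shows this, repeat it in the text of 3.1.

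No visit or procedure is added, and the delay disappears if Visit 7 is booked on D25 to D28. At nominal timing, the change fits the November 2015 to November 2016 first-visit plan without replacements. With both replacements and DMC meeting time, the shortest reading of that plan leaves little or no slack, and late visits could exceed it, so booking Visit 7 early in its window is the practical safeguard.

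Version 5.0 is dated 16 February 2017. If recruitment kept to plan, dosing was over by then, and the sentence would serve any later injections or a successor protocol.

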## Dosage/Dose Regimen for rAAV.hCNGA3 Phase I Trial

[figure not shown]

Figure 3: Schedule of dosing groups and intervals

### 3.2. Study Duration

- First patient first visit: November 2015
- Last patient first visit: November 2016
- Last patient last visit: November 2017
- Duration of trial participation per patient: 1 year plus 4-year follow-up period

After five years a clinical routine visit once per year and/or questionnaire will be performed (see also section 7.5) for long-term follow-up.

### 3.3. Participating Sites

The trial will be performed at the Centre for Ophthalmology, University of Tübingen. The site has a database of clinically and genetically characterized patients. In addition specialized retinal surgeons of the institution are familiar with subretinal interventions and have been trained in gene-therapeutic injections in an ongoing collaboration of the Centre for Ophthalmology with Oxford Eye Hospital, UK.

### 3.4. Number of enrolled patients

Nine patients will be enrolled in the trial. Drop-outs will only be replaced in case of non-ocular, non-treatment related reasons for the drop-out up to a number of two patients.

## 4. Study Population

### 4.1. Characterization of Patient Population

For this trial, adult patients of both genders with CNGA3-linked achromatopsia will be eligible (natural course and clinical symptoms see section 1.1.1.) with a BCVA  $\geq$  20/400 and discernable residual outer nuclear layer thickness in OCT scans of posterior pole. The precondition is the confirmed presence of mutation in the CNGA3 gene.

A) Patients will be pre-identified via the patient database of the Centre for Ophthalmology, University of Tübingen, they will be informed about the trial and invited for trial screening.

B) In addition, new patients to the clinic will be identified, informed about the trial and invited for trial screening. C) Patients from other hospitals, asking for trial participation will also be invited for screening.

Principally an intervention as early as possible in the course of the disease would be preferable, especially as the disease was initially thought to be non-progressive

[figure not shown]

because cone function was thought to be absent from birth. Yet, recent morphological in vivo studies established ACHM to be a slowly progressing degenerative retinal disease, and foveolar cone photoreceptor loss can be observed in most adult ACHM patients (Thiadens et al., 2010; Aboshiha et al., 2014; Greenberg et al., 2014; Sundaram et al., 2014; Yang et al., 2014). Therefore, it is deemed ethical to treat adult patients in this first interventional trial with the vector.

#### **4.2. Inclusion Criteria (Study Eye)**

- clinical diagnosis of achromatopsia
- $\geq 18$  years of age
- confirmed mutation in CNGA3
- BCVA  $\geq 20/400$
- a minimal outer nuclear layer thickness of  $10\mu\text{m}$  at  $3^\circ$  eccentricity in the study eye (normal =  $38\pm 6\mu\text{m}$ )
- ability to understand and willingness to consent to study protocol
- no infection with Human Immunodeficiency Virus (HIV)
- negative pregnancy test in women with childbearing potential (a woman who is two years post-menopausal or surgically sterile is not considered to be of childbearing potential)

#### **4.3. Exclusion Criteria**

- additional interfering eye conditions (e.g. uveitis, advanced cataract) in the study eye
- systemic conditions (e.g. coronary heart disease, autoimmune disorders) which may affect study participation or outcome measures
- current or recent participation in other study/or administration of biologic agent within the last three months
- recent (6 months) ocular surgery, intravitreal or subretinal implantation of a medical device
- known sensitivity to any compound used in the study
- contraindications to systemic immunosuppression
- subject/partner of childbearing potential unwilling to use adequate contraception for four months
- nursing or pregnant women
- any other cause that, in the investigator's opinion, renders potential subjects not suitable for the study
- mutations in another achromatopsia gene

- contraindications in view of the planned surgery (e.g. anaemia Hb<8g/dl, severe coagulopathy, severe blood pressure fluctuations)
- ocular opacity and mature cataract
- ocular infection with herpes simplex virus in medical history
- history of ocular malignancies
- disorders of the internal retina (e.g. retinal detachment in the patients history)
- glaucoma defined as damage of the optic nerve
- vascular retinal occlusion
- diabetic patients suffering from retinopathy and/or macula edema
- patients treated with oral corticoids within 14 days prior inclusion
- systemic illness or medically significant abnormal laboratory values in blood analysis including renal and hepatic functions at inclusion
- absence of vision on the other contralateral eye

